### Research grouping

Patients were divided into three groups based on the study's time phases and the differences in treatment they received after birth:

#### ICC+tracheal intubation group

From Jan.1, 2017 to Dec. 31, 2020. Umbilical cord clamping occurs within 20 s after birth. Infants are diagnosed with NRDS and receive a therapeutic dose of PS via tracheal intubation within the first 12 h after birth.

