## Abstract

**Background:**

Preventing early invasive mechanical ventilation (IMV) in preterm infants is critical for reducing bronchopulmonary dysplasia (BPD) and improving outcomes. While delayed cord clamping (DCC) enhances cardiopulmonary stability and minimally invasive surfactant administration (MISA) reduces IMV dependence, evidence on their combined efficacy in extremely preterm infants (<30 weeks gestation) with neonatal respiratory distress syndrome (NRDS) remains limited. We hypothesize that integrating DCC with MISA will synergistically reduce BPD incidence compared to immediate cord clamping (ICC) with either MISA or tracheal intubation-based surfactant delivery.

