### Participants

All infants participating in the study were selected using the same inclusion and exclusion criteria.

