#### ICC+MISA group

From Jan.1, 2021 to Dec. 31, 2024.Umbilical cord clamping is performed within 20 s after birth. Infants are diagnosed with NRDS and receive a therapeutic dose of PS via MISA within the first 2 h after birth.

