#### DCC+MISA group

From Aug. 31, 2025 to Oct. 31, 2027. Infants without contraindications to DCC, as determined by prenatal evaluation, receive immediate non-invasive respiratory support after birth. DCC is successfully performed for 60 s, followed by a diagnosis of NRDS. A therapeutic dose of PS is administered via MISA within the first 2 h after birth.

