### Data collection and diagnoses

Demographic data will include gestational age, birth weight, sex, multiple births, antenatal corticosteroid use, mode of delivery, maternal complications, Apgar score, and cord blood gas levels. Clinical data will encompass survival rates, required doses and timing of surfactant administration, blood gas measurements on the first day after birth, need for mechanical ventilation during hospitalization, duration of NCPAP/NIPPV, days on supplemental oxygen, hospitalization costs, and morbidity of BPD, pneumothorax, nasal trauma, pulmonary hemorrhage, hsPDA, IVH, PVL, blood culture-confirmed late onset sepsis, NEC, and ROP.

Pneumothorax will be diagnosed by the presence of air in the pleural cavity in a chest x-ray. Pulmonary hemorrhage will be diagnosed based on the gushing of bloody fluid from the upper airway or endotracheal intubation and when the chest x-ray is consistent with the relevant clinical findings. The diagnosis for hsPDA will be based on clinical signs and echocardiogram. IVH and white matter injury will be diagnosed by cranial ultrasound examination, and IVH will be graded by the Papile classification system. Blood culture-confirmed sepsis will be defined as clinical sepsis with evidence of pathogens in blood culture. NEC will be graded according to the modified Bell's classification system. The diagnosis and staging of ROP will be based on retinal examination by a consultant ophthalmologist.

Pneumothorax will be diagnosed radiographically by detecting air within the pleural cavity on chest radiography. Pulmonary hemorrhage is defined as acute onset of frank blood emanating from the upper airway or endotracheal tube, accompanied by radiographic evidence concordant with clinical manifestations. The diagnosis of hsPDA will be established through integration of clinical indicators and confirmatory echocardiography (13). IVH and PVL will be identified via standardized cranial ultrasonography, with IVH severity classified according to the Papile grading system (14). Culture-confirmed late-onset sepsis requires both compatible clinical signs and isolation of pathogenic microorganisms from blood cultures. NEC will be staged using the modified Bell's classification criteria (15). ROP diagnosis and staging will be determined through comprehensive retinal evaluations performed by a certified ophthalmologist.

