DCC not only enhances the transfer of blood from the placenta to the fetus, improving hemoglobin reserves in premature infants, but it also stabilizes the establishment of pulmonary circulation in the early postnatal period. Since placental circulation provides 30%–50% of cardiac blood flow, immediate clamping of the umbilical cord can lead to a significant drop in venous return and cardiac output. DCC facilitates a smoother transition until premature infants can establish effective pulmonary ventilation and circulation. Thus, DCC serves as a crucial component of early respiratory and circulatory management for these infants. This study aims to determine whether the simultaneous application of DCC and MISA further enhances survival and prognosis in premature infants. Given our recent implementation of DCC for infants born before 30 weeks, we designed a NICU quality improvement study to evaluate the efficacy of DCC combined with MISA by comparing prospective and retrospective cohorts.

Despite the potential of this study, there are some limitations to consider. As a quality improvement study, data for the ICC and MISA and ICC and tracheal intubation groups were collected retrospectively, which may introduce biases due to variations in hospitalization years and treatment approaches. Furthermore, the retrospectively collected data are based on the diagnosis, treatment, and evaluation conducted by clinicians, and there may be variations in this process. To minimize these discrepancies, we limited the study to preterm infants from the past six years for the retrospective cohort. Additionally, both the prospective and retrospective cohorts adhered to the same inclusion and exclusion criteria to reduce intergroup differences and enhance the validity of the conclusions.

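### Infants enter the intubation group if given surfactant within 12 h, but the MISA groups only within 2 h, so both contrasts with intubation compare differently selected infants

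*Protocol article*

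**What the plan says.** Under Research grouping, the protocol article states: "Patients were divided into three groups based on the study's time phases and the differences in treatment they received after birth". The three definitions that follow each contain a surfactant window:

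- ICC+tracheal intubation (2017–2020): infants "receive a therapeutic dose of PS via tracheal intubation within the first 12 h after birth".
- ICC+MISA (2021–2024): infants "receive a therapeutic dose of PS via MISA within the first 2 h after birth".
- DCC+MISA (August 2025 to October 2027): "A therapeutic dose of PS is administered via MISA within the first 2 h after birth".

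The Inclusion criteria and Exclusion criteria sections give no time limit for diagnosing NRDS or giving surfactant. The Participants section states: "All infants participating in the study were selected using the same inclusion and exclusion criteria". The limitations paragraph of the Discussion presents this as a protection against bias, saying that "both the prospective and retrospective cohorts adhered to the same inclusion and exclusion criteria to reduce intergroup differences". Data collection and diagnoses lists "required doses and timing of surfactant administration" among the clinical data.

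The hypothesis in the Abstract sets DCC with MISA "compared to immediate cord clamping (ICC) with either MISA or tracheal intubation-based surfactant delivery", and the Conclusion again names the intubation group as a comparator.

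**The concern.** Because treatment received is part of group membership, the surfactant window works as an entry rule, and that rule differs between groups. Time to first surfactant is a post-birth event that may be related to how early and how severely respiratory distress develops. Infants treated at 2–12 h could be milder cases whose disease progressed slowly, or infants in whom non-invasive support failed late. Either way, the intubation group can contain them and the MISA groups cannot.

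A difference in BPD or survival between a MISA group and the intubation group would then reflect partly the regimen and partly who was allowed in. The intubation group supplies 222 of the 518 planned records (222 + 222 + 74). A reader who relies on the limitations paragraph would believe that selection had been aligned across the cohorts.

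**Working it through.** **1. The definitions side by side.** Take an infant who meets every listed criterion and first receives surfactant at 5 h.

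| Birth year and route | Window | Analysed? |
|---|---|---|
| 2019, intubation | 12 h | Yes, ICC+intubation |
| 2022, MISA | 2 h | No group |
| 2026, MISA after DCC | 2 h | No group |

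Of the three pairwise contrasts, the two involving intubation are affected. DCC+MISA versus ICC+MISA has 2 h on both sides.

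**2. The plan's own sample size.** From Sample size calculation: p1 = 0.29 (ICC+MISA), p2 = 0.14 (DCC+MISA), k = 3, z-values 1.96 and 0.84.

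n2 = (1.96 + 0.84)² × [0.29 × 0.71/3 + 0.14 × 0.86] / 0.15² = 7.84 × 0.18903 / 0.0225 = 65.87, rounded up to 66.

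Then 3 × 66 = 198. With 10% loss, 66/0.9 gives 74, and 3 × 74 = 222. The stated figures reproduce and concern only the unaffected contrast. The 222 for the intubation group is set without a calculation of its own.

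**3. Possible bias (illustration).** If a share s of the intubation group was treated at 2–12 h, and their BPD risk differs by d from those treated by 2 h, the group's rate shifts by s × d. The article gives neither quantity. With s from 10% to 50% and d from 10 to 20 points (assumed), the shift runs from 0.10 × 10 = 1 point to 0.50 × 20 = 10 points, in either direction. Suppose there is no true regimen effect and the common rate is 29%. In a two-sided two-proportion test of 222 against 222 (normal approximation, pooled null variance), a 5-point shift is significant about 20–22% of the time and a 10-point shift about 60–70%, against a nominal 5%.

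**4. Precision cost of a common 2 h window.** Half-width = 1.96 × √[p1(1 − p1)/n1 + p2(1 − p2)/n2]. Here p1 = 0.70 is the intubation rate quoted in Sample size calculation, and n1 is the number of intubation infants kept. The comparator is ICC+MISA (0.29, n2 = 222) or DCC+MISA (0.14, n2 = 74). The retained shares are assumptions.

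| Share of 222 kept | n1 | Half-width vs ICC+MISA | Half-width vs DCC+MISA |
|---|---|---|---|
| 100% | 222 | 8.5 points | 9.9 points |
| 50% | 111 | 10.4 points | 11.6 points |
| 25% | 56 | 13.4 points | 14.4 points |

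For example, the first entry is 1.96 × √(0.21/222 + 0.2059/222) = 0.085. The planning differences are 70 − 29 = 41 points and 70 − 14 = 56 points.

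**5. If the true difference is smaller.** The 70% and 29% come from 20 and 31 infants. The approximate 95% interval for their difference is 41 ± 1.96 × √(0.21/20 + 0.2059/31) × 100 = 41 ± 25.7 points, so a gap of 16 points is not excluded. With an assumed intubation rate of 45% against 29% in 222 ICC+MISA infants, power is Φ(0.16/SE − 1.96), using the same unpooled SE. This gives 94% for n1 = 222, 81% for 111 and 59% for 56.

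**The case against.** The strongest defence is that timing belongs to the regimen. The article calls the 2017–2020 treatment conventional and frames the study as before and after implementation. If conventional care gave surfactant later, 12 h describes that care. This does not rescue the comparison: a regimen comparison would still have to count MISA-era infants treated after 2 h, and the definitions drop them.

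A second defence is that the statements about shared criteria are literally true, since the listed criteria are common and the windows sit under a different heading. That is correct, so the fault in those sentences is overstatement. The limitations paragraph does admit bias from calendar years and treatment approaches, but it does not disclose the unequal windows.

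Third, the Statistical analysis section plans logistic regression allowing for confounders in general, as well as the sensitivity model built from baseline variables with P < 0.1. Surfactant timing could therefore be modelled. No covariate, however, restores infants whom the group definition excluded.

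Several limits on the point stand:

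- The bias is not quantified, and a shift of 1–10 points would not reverse differences as large as 41 or 56 points.
- The 222 is a target. If more than 222 eligible intubation infants exist, the precision loss could be smaller than shown.
- The contrasts with intubation are also confounded by calendar era, which no choice of window removes.
- A 2 h restriction may itself select earlier or more severe disease from 2017–2020.

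**Conclusion.** The concern holds. Followed as written, the group definitions produce differently selected infants for both contrasts with the intubation group, and the protection the Discussion cites does not cover this. The mismatch is certain from the text; its effect on the results is not, because the number and risk of infants treated at 2–12 h are not given. The shifts of 1–10 points and the false-positive rates above rest on assumed shares and risk differences.

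The powered comparison is untouched, so this does not threaten the study's main sample-size argument. It does weaken a comparison that the hypothesis and conclusion rely on. Unlike confounding by era, it can be avoided. At the planning rates a common 2 h window is affordable even if only a quarter of the intubation infants remain; at an assumed 45% intubation rate, the same loss would cut power against ICC+MISA to about 59%.

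**What to change.** For every contrast with the intubation group, apply one time-to-surfactant window when selecting records: 2 h in all groups, or 12 h in all groups where the records allow. Show the analysis under the stated windows beside it, and report time to first surfactant by group. In Participants and in the limitations paragraph, state that the listed criteria are common but the group definitions use different surfactant windows. Leave DCC+MISA versus ICC+MISA as it is. The change concerns which records are analysed, not when any infant is treated.

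The cost is some wording and one extra record selection, since timing is already collected. A 2 h window leaves fewer intubation infants unless more records are available, and it may favour earlier or more severe disease, which is why both analyses should appear. A 12 h window needs additional MISA-era records. Confounding by calendar era remains in either case.

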#### ICC+MISA group

From Jan.1, 2021 to Dec. 31, 2024.Umbilical cord clamping is performed within 20 s after birth. Infants are diagnosed with NRDS and receive a therapeutic dose of PS via MISA within the first 2 h after birth.

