#### Exclusion criteria

① Premature infants who have received tracheal intubation prior to the use of PS due to resuscitation or other reasons shortly after birth;② Premature infants with identified or confirmed congenital abnormalities (such as fetal edema, chylothorax, or neuromuscular disease) or severe birth complications (including hemorrhagic shock, air leakage, or early-onset sepsis) that impact respiratory function;③ Newborns who discontinue treatment or have incomplete information;④ Newborns involved in other intervention research studies.

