#### Quality improvement-related indicators

The rate of first-time pulmonary surfactant administration via MISA among all preterm infants with a gestational age of 23–29 + 6 weeks admitted to the NICU and the trend of this rate changing over years.The success rate of MISA (defined as the completion of pulmonary surfactant administration under non-invasive support, without early termination of administration or switching to tracheal intubation for administration).The rate of DCC among all preterm infants with a gestational age of 23–29 + 6 weeks admitted to the NICU and the trend of this rate changing over years.

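### Both MISA groups are defined by a dose delivered via MISA, so a stopped or converted attempt from 2021 onward fits no group, which may favour MISA in the comparison with intubation

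*Protocol article*

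**What the plan says.** All references are to the protocol article.

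- **Research grouping:** infants are "divided into three groups based on the study's time phases and the differences in treatment they received after birth".
- **ICC+MISA group (2021–2024):** infants "receive a therapeutic dose of PS via MISA within the first 2 h after birth".
- **DCC+MISA group (Aug. 2025–Oct. 2027):** "A therapeutic dose of PS is administered via MISA within the first 2 h after birth". Entry also requires completed cord management: "DCC is successfully performed for 60 s, followed by a diagnosis of NRDS".
- **ICC+tracheal intubation group:** "From Jan.1, 2017 to Dec. 31, 2020"; infants "receive a therapeutic dose of PS via tracheal intubation within the first 12 h after birth".
- **Quality improvement-related indicators:** a successful MISA is one completed on non-invasive support, "without early termination of administration or switching to tracheal intubation for administration". Failed attempts are therefore expected, but they appear only in this indicator.
- **Exclusion criteria, item 1:** "Premature infants who have received tracheal intubation prior to the use of PS due to resuscitation or other reasons shortly after birth".

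The Statistical analysis section describes no analysis by attempted route. The limitations paragraph of the Discussion does not mention this selection.

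**The concern.** Whether MISA is completed becomes known only after the attempt has begun. Defining the MISA groups by completion makes membership depend on an event after the start of treatment, and that event may be related to how ill the infant is. The 2017–2020 group was not screened in this way: an infant who would have failed MISA simply received surfactant through the tube and stays in.

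If failures do worse than completers, the MISA groups lose some of their poorer outcomes and the intubation group does not. That would lower BPD and raise survival in the MISA groups without any treatment effect. The comparison matters because the hypothesis in the Abstract and the Conclusion both set DCC+MISA against the intubation group as well as against ICC+MISA. Adjustment for baseline variables cannot repair this, because the missing infants are not in the data set.

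**Working it through.** **1. Where does a stopped or converted MISA attempt go?** Take an infant born in 2021 or later who meets the inclusion criteria.

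| Group | Condition | Does the infant fit? |
|---|---|---|
| ICC+MISA | therapeutic dose received via MISA within 2 h | No: the dose was not delivered that way |
| DCC+MISA | the same, after completed DCC | No, for the same reason |
| ICC+tracheal intubation | born 2017–2020 | No: the period has closed |

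An infant from 2017–2020 who would have failed MISA does fit the third group.

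**2. The plan's own figures.** Sample size calculation uses p1 = 0.29 and p2 = 0.14, with ratio 3:

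n2 = (1.96 + 0.84)² × [0.29 × 0.71/3 + 0.14 × 0.86] / 0.15² = 65.87, so 66, and n1 = 3 × 66 = 198. With 10% loss, 66/0.9 gives 74, and 3 × 74 = 222.

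The stated figures reproduce, and this point changes none of them. The 15-point planned effect belongs to DCC+MISA versus ICC+MISA.

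**3. MISA versus intubation, assuming no true effect.** Let P be BPD in all attempted infants and f the MISA failure rate. P = 0.29 is the document's figure for an earlier MISA group, used here for all attempts. The failure rate and the risk in failures are assumed, because the document gives neither.

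*(a) Failures at RR times the completers' risk:* completers' rate = P / (1 − f + f × RR).
- f = 0.05, RR = 1.5: 0.29/1.025 = 28.3%, a spurious 0.7 points.
- f = 0.10, RR = 2: 0.29/1.10 = 26.4%, a spurious 2.6 points.
- f = 0.20, RR = 2: 0.29/1.20 = 24.2%, a spurious 4.8 points.

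With 222 versus 222 infants and an unadjusted normal-approximation test, the chance of a significant result favouring MISA is about 4% in the first case and 21% in the last, against a nominal 2.5%.

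*(b) BPD of 70% in failures, borrowed from the earlier intubation group (n = 20):* completers' rate = (0.29 − 0.70f) / (1 − f).
- f = 0.05: 0.255/0.95 = 26.8%, a spurious 2.2 points.
- f = 0.10: 0.220/0.90 = 24.4%, a spurious 4.6 points.
- f = 0.15: 0.185/0.85 = 21.8%, a spurious 7.2 points.

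Scenario (b) is the harsher one. It implies failures at 0.70/0.268 = 2.6 to 0.70/0.218 = 3.2 times the completers' risk.

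**4. DCC+MISA versus ICC+MISA.** Both groups carry the same MISA filter. With no true effect and equal failure rates, the two completer rates are identical and the bias is zero. If failure is 15% in one period and 5% in the other:
- RR = 2: 0.29/1.05 − 0.29/1.15 = 27.6% − 25.2% = 2.4 points.
- 70% in failures: 26.8% − 21.8% = about 5 points.

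The period with more failures looks better. If failure falls over time, the shift is against DCC; if it rises, the shift favours DCC.

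**The case against.** The best defence is that the wording describes the regimen rather than a completion test. The article says DCC must be successfully performed but attaches no such word to MISA. It plans to count failed attempts, and a full protocol or analysis plan might say where they are analysed. That makes an intention to drop these infants unproven. It does not supply a group for them: assignment is by treatment received, and the definitions are fixed in this document.

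Several stronger inferences are tempting, but the document does not support them:

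- **That exclusion 1 also removes converted infants.** Every infant in the intubation group is intubated before surfactant in order to receive it. Exclusion 1 must therefore mean intubation for other purposes, or it would empty that group. The point needs only a clarification.
- **That any fall in heart rate or saturation removes an infant.** Under Quality control, such an event pauses instillation, which resumes until the dose is complete. Only a true stop or conversion matters.
- **That the intubation group keeps all its sickest infants.** The spontaneous-breathing criterion and exclusion 1 apply in every period. What the intubation group lacks is only the filter on MISA completion.
- **That the MISA success rate is 100% by construction.** This would follow only if it were computed within the enrolled MISA groups, and the document does not restrict it so.
- **That 2–7 points should be read against the planned 15.** Those points concern MISA versus intubation; the 15 concern the comparison in which the filter is shared.

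**Conclusion.** The concern holds for the comparison with intubation. Taken literally, the grouping rules select MISA completers from 2021 onward and leave stopped or converted attempts without a group, while the 2017–2020 group is not filtered in the same way.

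The direction, towards MISA, rests on failures being sicker than completers. That is plausible, but the document does not show it. The size is unknown: the 0.7–4.8 and roughly 2–7 point ranges for BPD are illustrations on assumed inputs, and no figure can be put on survival.

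The powered DCC+MISA versus ICC+MISA comparison is largely protected. It would shift only if failure rates differ by period, by about 2.4 to 5 points for 15% versus 5%. The requirement of completed DCC is a separate selection and is not counted here.

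**What to change.** - Define both MISA groups, for analysis, by the first surfactant route attempted within the stated window, whether or not the dose was completed that way.
- Keep infants whose MISA was stopped or converted in their MISA group for BPD, survival and all secondary outcomes.
- State that exclusion 1 does not cover intubation following a MISA attempt.
- Compute the MISA success rate over all attempts, and report the number of failures by period.
- Report the delivered-by-MISA set as a sensitivity analysis.

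The cost is a few sentences in Research grouping and Exclusion criteria, plus some extra chart abstraction in a single unit. The BPD rate in the MISA groups may look less favourable. These changes concern group definition and analysis only, and do not alter how any infant is treated.
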